# The efficacy and safety of herbal medicine BHH10 in postmenopausal women with osteoporosis: study protocol for a phase II, multicenter, randomized, double-blinded, placebo-controlled clinical trial

**DOI:** 10.1186/s13063-018-2854-6

**Published:** 2018-09-10

**Keywords:** Osteoporosis, Postmenopausal women, Herbal medicine, BHH10, Protocol

## Abstract

**Background:**

Osteoporosis is becoming more prevalent in aging societies worldwide, and the economic burden attributable to osteoporotic fractures is substantial. The medications presently available to treat osteoporosis have side effects, and the development of safer and more effective treatments is urgently needed. The aim of this study is to evaluate the efficacy and safety of BHH10, a traditional Korean herbal medicine, in the treatment of postmenopausal osteoporosis.

**Methods/Design:**

This is a phase II, multicenter, randomized, double-blinded, placebo-controlled clinical trial and will include 168 postmenopausal women aged 55 years and older with osteoporosis. The participants will be recruited competitively from two sites of the Acupuncture and Moxibustion Department of Kyung Hee University Hospital of Korean Medicine, either Hoegidong or Gangdong in Seoul, Korea. Participants will be assigned randomly to one of two groups, the BHH10 group or the placebo group, in a 1:1 ratio, and will have five scheduled visits. Participants will take two tablets of BHH10 or placebo three times daily for 12 weeks. The primary efficacy outcome is the change in bone mineral density at the lumbar spine (L1–4) between baseline (visit 1) and 12 weeks after randomization (visit 5). Other outcome variables include changes in bone turnover markers, the Deficiency Syndrome of the Kidney Index, EuroQol five-dimension questionnaire score, and laboratory parameters, as well as adverse events.

**Discussion:**

To our knowledge, this will be the first clinical trial to assess the efficacy and safety of BHH10 in postmenopausal women with osteoporosis. It is anticipated that the results will contribute to the development of traditional herbal medicines that can be used to treat osteoporosis in postmenopausal women in Korea. If the superiority of BHH10 over placebo is demonstrated, this study could provide the foundation for a phase III clinical trial. The results of the study will be published in a peer-reviewed journal.

**Trial registration:**

Clinical Research Information Service, KCT0001842. Registered on 14 March 2016.

**Electronic supplementary material:**

The online version of this article (10.1186/s13063-018-2854-6) contains supplementary material, which is available to authorized users.

## Background

Osteoporosis is a systemic skeletal disease characterized by decreased bone mass and altered microstructure that leads to bone fragility and an increased risk of fractures [1]. As osteoporosis is easily overlooked due to the lack of subjective symptoms, the prevalence of osteoporosis is higher in aged people. In 2010, more than 99 million individuals aged 50 years or older in the U.S. alone were estimated to have osteoporosis or low bone mass, and this number is projected to increase by 19% by 2020 and by 32% by 2030 [2]. The data sharing statements are detailed in Table 1.

**Table 1 Tab1:** Data sharing statements

ICMJE requirements	Answer
Will individual participant data be available (including data dictionaries)?	Yes
What data in particular will be shared?	Individual participant data behind the results reported in this article, after deidentification (text, tables, figures, and appendices)
What other documents will be available?	Study protocol
When will data be available (start and end dates)?	Beginning 3 months and ending 5 years following publication of the research
With whom?	Investigators whose proposed use of the data has been approved by an independent review committee identified for this purpose
For what types of analyses?	To achieve the aims in the approved proposal.
By what mechanism will data be made available?	Proposals should be directed to [contact]; to be given access, data requestors must sign a data access agreement

The prevalence of osteoporosis is particularly high in women after the menopause. Approximately 80% of patients with osteoporosis are female and postmenopausal. The hormonal changes stimulate ligands of the receptor activator of nuclear factor-κβ to promote osteoclastogenesis [3]. The fifth Korean National Health and Nutrition Examination Survey in 2010 reported a high risk of osteoporotic fracture in 37.7% of postmenopausal women aged 50 years or older [4]. Aggregated data for women aged 55 years or older from 2000 to 2011 in the U.S. show that the hospitalization costs for osteoporotic fractures are greater than those for myocardial infarctions, breast cancer, or strokes [5].

Many pharmacological agents, such as bisphosphonates, alendronate, risedronate, and denosumab, are used to treat postmenopausal osteoporosis. However, the agents most commonly used are inconvenient to take and compliance is often poor [6]. For example, an oral bisphosphonate tablet must be taken in the morning before breakfast with plenty of water and the patients must remain seated for 30 to 60 min afterwards, and not eat during this time [7]. Furthermore, many patients stop taking the medication because of concerns about side effects such as atypical femoral fractures, osteonecrosis of the jaw, and irritation of the gastrointestinal tract [8].

There is an increasing need for agents that are safer and more effective for the treatment of osteoporosis. According to traditional Korean medicine, kidney dysfunction can cause osteoporosis by inhibiting bone metabolism and decreasing the level of estrogen [9]. Herbal medicines targeted at the kidney, such as *jasinhwan*, are already used to treat osteoporosis [10]. BHH10 is an herbal medicine derived from *jasinhwan* and consists of the roots of *Astragalus membranaceus* (Mongolian milkvetch), twigs of *Cinnamomum cassia* (Chinese cassia or Chinese cinnamon), and the bark of *Phellodendron amurense* (Amur cork tree). BHH10 has been shown to regulate bone resorption and improve bone mineral density (BMD) without toxic effects in ovariectomized rats [11].

This placebo-controlled study is evaluating the efficacy and safety of BHH10 in the treatment of postmenopausal osteoporosis by measuring changes in BMD, levels of bone turnover markers, the Deficiency Syndrome of the Kidney Index (DSKI), and the EuroQol five-dimension questionnaire (EQ-5D) score, as well as adverse events.

The study protocol was developed in accordance with the 2013 Standard Protocol Items: Recommendations for Interventional Trials (Additional file 1).

## Methods/Design

### Objective

The primary aim of this study is to determine if treatment with BHH10 for 12 weeks results in a greater increase in BMD at L1–4 than those who receive a placebo. The secondary outcomes are:any significant differences in femoral BMD, bone turnover marker levels, DSKI, and EQ-5D score in the group receiving BHH10 compared to the group receiving the placebo after 12 weeks of treatmentto determine if there is a causal relationship between the primary outcome and the DSKI or EQ-5D scorewhether BHH10 is a safe treatment based on laboratory parameters, vital signs, and electrocardiography (ECG).

### Design and setting

This study is a phase II multicenter, randomized, placebo-controlled clinical trial with two parallel groups. Participants who voluntarily sign informed consent and are eligible for this study will be assigned randomly to one of two groups (the BHH10 or the placebo group) in a 1:1 allocation. Patients will take two tablets of BHH10 or placebo three times daily for 12 weeks.

#### Recruitment strategy

The study participants were recruited competitively from two sites of the Acupuncture and Moxibustion Department of Kyung Hee University Hospital of Korean Medicine, either Hoegidong or Gangdong in Seoul, Korea. A total of 168 postmenopausal women with osteoporosis were recruited via broadcast media, newspapers, posters, and the Internet homepages of the participating hospitals, as well as advertisements placed in nearby welfare centers. Recruitment started in March 2016 and the accrual target was reached in April 2018.

#### Study plan

This study will be conducted in two phases (Fig. 1):Screening (2 weeks): Trained researchers in the hospital will explain this trial to and seek written informed consent from potentially eligible patients. Patients who agree to participate in the study will undergo BMD measurements, laboratory investigations, and an ECG. The results of these tests will be conveyed by telephone and patients who meet the inclusion criteria will be randomized within 2 weeks after the screening visit.Treatment (12 weeks): On the second visit, patients will be randomly assigned to one of the two groups (the BHH10 group or the placebo group) and supplied with their allocated investigational drugs after completing the DSKI and EQ-5D questionnaires. Participants will take two tablets of BHH10 or placebo three times daily for 12 weeks. Additional visits will be made at monthly intervals during the 12 weeks of treatment. A total of four visits will be made during the treatment period. A blood test will be conducted 8 weeks after randomization (visit 4). BMD measurements, blood and urine tests, and an ECG will be performed 12 weeks after randomization (visit 5).

**Fig. 1 Fig1:**
[figure not shown]
Flow chart of the study

### Types of participant

#### Inclusion criteria

Participants must be women who meet the following criteria:Ambulatory and aged 55–85 yearsPostmenopausal (at least 12 months since the last menstrual period)BMD should be below −2.5 standard deviationsWilling to participate and sign a consent form after being given a detailed explanation of the trial

#### Exclusion criteria

Participants will be excluded if any of the following conditions are satisfied:Alkaline phosphatase more than twice the upper limit of normalLiver disease (aspartate transaminase or alanine transaminase more than twice the upper limit of normal)Kidney disease (creatinine > 2.0 mg/dL)Hypercalcemia (calcium > 10.5 mg/dL)Uncontrolled chronic disorders that could affect bone metabolism (liver disease, alcoholism, primary hyperparathyroidism, or malignancy)Pharmacotherapy for osteoporosis (except calcium or vitamin D) in the previous 3 monthsInjection of an agent for osteoporosis in the previous 6 monthsSystemic administration of an agent that may affect calcium metabolism in bone, such as a systemic corticosteroid or diuretic, for more than 6 months (subjects who have not received forbidden drugs except contraceptive injections within the previous 3 months before screening may be eligible to participate)Metabolic bone diseases other than osteoporosisA mental disorder likely to affect compliance with the requirements of the trial

### Randomization and allocation concealment

For randomization, an independent blinded statistician will generate random numbers using the SAS randomization program (version 9.4; SAS Institute, Inc., Cary, NC, USA). The manufacturer will supply the hospital with investigational drugs in consecutively numbered drug containers with identical packaging to conceal treatment allocation. Blinded researchers in each hospital will enroll and assign participants to one of the two study groups.

### Blinding

The participants, outcome assessors, study monitors, data managers, and statisticians will be blinded to treatment allocation. If possible, the study participants will be advised to avoid discussing the investigational drugs with other participants. Blinding will be maintained until the 168 participants have completed the study. The success of double-blinding will be assessed at the final visit. The database will then be locked.

An emergency code for each individual has been provided to study researchers and will be disclosed only if it must be known whether a patient is receiving BHH10 or the placebo to manage a serious adverse event.

### Intervention

The total dose of each tablet of BHH10 is 800 mg, of which 400 mg is 30% ethanol herbal extract (Fig. 2). The herbal extract was obtained from the roots of *A. membranaceus*, the twigs of *C. cassia*, and the bark of *P. amurense* in a ratio of 2:2:1. All plant materials and the samples were deposited in the herbarium of Quality Control of the Hanpoong Pharm and Foods Co., Ltd. (Junju, South Korea). The raw materials were extracted twice with 30% ethanol and vacuum-dried to produce the BHH10 extract (yield, 9.72%).

**Fig. 2 Fig2:**
[figure not shown]
Appearance of investigational drug (BHH10)

A high-performance liquid chromatography analysis was performed to quantify the chemical constituents of the BHH10 herbal extract. The herbal extract was controlled to contain more than 1.15 mg/g of cinnamic acid, 0.26 mg/g of formononetin, and 10.67 mg/g of berberine. The purity test, including heavy metal tests, residual pesticide tests, and a microbial limit test, was conducted according to the Korea Pharmacopeia. The extract is tested for the presence of heavy metals, lead, arsenic, DDT, benzene hexachloride aldrin, dieldrin, endrin, total number of aerobic microorganisms, and microorganism counts (including fungi, *Escherichia coli*, *Salmonella*, *Pseudomonas aeruginosa*, and *Staphylococcus aureus*).

The placebo tablets contain cellulose, corn starch, diluting agents, and food coloring to match the BHH10 tablets (Fig. 3). The BHH10 and placebo tablets are manufactured to be identical in appearance in terms of shape, color, size, smell, and taste. The BHH10 and placebo tablets are manufactured at Hanpoong Pharm and Foods Co., Ltd. in accordance with Korean Good Manufacturing Practices.

**Fig. 3 Fig3:**
[figure not shown]
Appearance of investigational drug (placebo)

The study participants will take two tablets of BHH10 or placebo, three times daily for 12 weeks. The dosage was determined by reference to preclinical studies [11, 12].

During the 12 weeks of treatment, participants will comply with the study protocol by visiting the clinic every month and completing their scheduled examinations. Unused tablets will be returned and counted at visits 3, 4, and 5. If a participant is unable to take the allocated investigational drug because of serious adverse event, the researchers can alter the dose or frequency according to internal guidelines.

#### Concomitant and forbidden treatments

Drugs that have been taken for an indication other than osteoporosis for more than 30 days before the screening visit may be continued during the study period. Continuation of the same doses of health functional foods, such as calcium or vitamin D, are permitted in this trial only if they have been taken continuously in the 3 months before the screening visit. Prohibited drugs include agents that can affect BMD, such as other medications for osteoporosis, steroids, carbamazepine, phenytoin, phenobarbital, heparin, warfarin, thyroid hormones, gonadotropin-releasing hormone agonists, depot-medroxyprogesterone acetate, anticancer drugs, cyclosporine A, antidepressants, aluminum-containing antacids, aromatase inhibitors, anti-tuberculosis drugs, thiazolidinedione, proton pump inhibitors, antiretroviral drugs, and thiazide diuretics. Participants who have taken or need to take any of these medications will be withdrawn from the study.

### Outcomes

The measurement points of each evaluation index are shown in Fig. 4.

**Fig. 4 Fig4:**
[figure not shown]
Standard Protocol Items: Recommendations for Interventional Trials (SPIRIT) schedule of enrollment,interventions, and assessments

#### Primary outcome measurement

The primary outcome will be the change in BMD at the lumbar spine (L1–4) between baseline (visit 1) and 12 weeks after randomization (visit 5). BMD will be examined by dual-energy X-ray absorptiometry. Both participating institutions use the same type of X-ray machine (Lunar Prodigy, GE Medical Systems Lunar, Madison, WI, USA).

#### Secondary outcome measurements

##### Femoral BMD

The change in femoral BMD between at baseline (visit 1) and after treatment (visit 5) will be calculated using the lowest values at the femoral neck and total hip.

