### Sample size

The primary null hypothesis of this study is that there is no difference in the change in BMD at the lumbar spine (L1–4) between the BHH10 and placebo groups after 12 weeks of treatment. In view of the results of a similar study of herbal medicine in postmenopausal women with osteoporosis [16], a mean difference of 0.047 ± 0.097 between the experimental group and control group was assumed. With a 5% significance level and a power of 80%, it was calculated that a sample size of 66 patients per group would be necessary. Allowing for a dropout rate of 20%, a sample size of 168 participants (84 in each group) has been included.

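### Femoral BMD change is built from the lowest of femoral neck and total hip without fixing site or scale, so it cannot be read as an effect at either site and a one-site effect is diluted

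*Protocol article*

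**What the plan says.** Under Objective, the first secondary aim is to look for "any significant differences in femoral BMD, bone turnover marker levels, DSKI, and EQ-5D score" between BHH10 and placebo after 12 weeks. The Femoral BMD section defines that endpoint as a change from visit 1 to visit 5 which "will be calculated using the lowest values at the femoral neck and total hip". This one sentence is all the article gives on how the femoral value is formed.

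Two other places matter for comparison. The primary outcome is tied to a fixed region, L1–4 of the lumbar spine. The inclusion criteria state the BMD threshold in standard deviations, so two scales, absolute density and SD score, are in play. The femoral rule does not say on which of them the lowest value is judged.

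**The concern.** A change score describes a place in the skeleton only if the same place is measured twice. Taking the lower of two sites does not guarantee that. A woman whose neck reads lower at visit 1 and whose total hip reads lower at visit 5 contributes a hip value minus a neck value.

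Two things are at stake. The first is interpretation: the group mean is a blend of neck and hip changes, with weights set by how often each site happens to be lower, so it cannot be reported as an effect at a named site. The second is sensitivity: if BHH10 acts mainly at one site, women whose lower value comes from the other site pull the estimate towards zero. Femoral BMD is the only BMD outcome listed besides the primary one, so it is the natural place to look for support of a lumbar result. The open wording also leaves several definitions available once the data are seen.

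**Working it through.** **1. The plan's own figure.** The article gives no calculation for femoral BMD. For the primary endpoint it assumes "a mean difference of 0.047 ± 0.097 between the experimental group and control group was assumed" and concludes that "a sample size of 66 patients per group would be necessary". With a two-sided 5% level (sidedness is not stated) and 80% power, n = 2 × (1.960 + 0.842)² × (0.097/0.047)² = 66.9, so 67 per group, and 67/0.80 = 83.75, so 84 per group and 168 in total. The stated figures are reproduced to within one patient per group. The femoral rule does not enter them.

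**2. Readings that the sentence allows.** (a) The lower site is picked afresh at each visit. (b) The site that is lower at baseline is kept. (c) The lowest reading is taken at each site, giving two results. Reading (a) is the most natural, since a single femoral BMD change is described.

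**3. Does re-picking create a false change?** Let N0, T0 be neck and total hip at visit 1 and N1, T1 at visit 5, all on one scale, with change C = min(N1,T1) − min(N0,T0). Suppose N0 is the lower baseline value.
- Since min(N1,T1) ≤ N1, C ≤ N1 − N0.
- If T1 is the lower value at visit 5, C = T1 − N0 ≥ T1 − T0, because N0 ≤ T0.

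So C always lies between the two observed site changes; 400,000 random draws gave no exception. With no true change, simulation gave a mean of C of about 0 and an SD no larger than at one fixed site (for example 0.136 against 0.142).

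**4. Inputs for the size of the effect (assumptions, SD-score units).** Mean hip-minus-neck gap μ from 0 to 1.0; between-woman SD of that gap σ from 0.5 to 0.7; scan error e from 0.1 to 0.3 per reading. If the hip were the lower site on average, the hip and neck results would swap.

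**5. Site switching under (a), no true change.** Simulated: about 2% (μ = 1.0, σ = 0.5, e = 0.1) to about 30% (μ = 0, σ = 0.5, e = 0.3) of women. By step 3, this is not a measure of error.

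**6. Dilution under (a).** Let s = √(σ² + 2e²) and h(m) = m·Φ(m/s) + s·φ(m/s). Since E[min(N,T)] = E[N] − E[max(0, N − T)], a true gain δ gives an expected change of
- hip only: h(−μ) − h(−μ − δ)
- neck only: δ − [h(−μ + δ) − h(−μ)]
- both sites equally: δ

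Example with δ = 0.30, μ = 0, σ = 0.7, e = 0.3: s = √(0.49 + 0.18) = 0.819; h(0) = 0.327; h(−0.30) = 0.198; the hip-only gain appears as 0.128.

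| μ | σ | e | 0.30 at hip only | 0.30 at neck only | 0.30 at both |
|---|---|---|---|---|---|
| 0 | 0.5 | 0.1 | 0.116 | 0.116 | 0.30 |
| 0 | 0.7 | 0.3 | 0.128 | 0.128 | 0.30 |
| 1.0 | 0.5 | 0.1 | 0.004 | 0.284 | 0.30 |
| 1.0 | 0.7 | 0.3 | 0.024 | 0.255 | 0.30 |

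Over the whole grid: hip only about 0.00 to 0.13, neck only about 0.12 to 0.28. Simulation agrees.

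**7. Reading (b).** Selecting on a low baseline reading adds an expected rise of 2e²·φ(μ/s)/s, which is 0.002 to 0.11 over the grid and is the same in both arms. Dilution remains: the contrast between arms is δ times the share of women whose lower baseline site is the affected one. With μ = 0 that is 0.30 × 0.5 = 0.15.

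**8. Mixed scales.** If the site is picked on SD score but the change is taken in g/cm2 (assuming 0.12 g/cm2 per SD unit and e from 0.1 to 0.2), the SD of change relative to a single site is 0.96 to 1.05 for a site offset of 0.02 g/cm2, 1.05 to 1.4 for 0.05, and 1.2 to 2.3 for 0.10. The mean change stays at about 0.

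**The case against.** The strongest reply has four parts.

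- **No artefact.** A reader might infer that part of the computed change is spurious because the site can switch. On one scale this is wrong, as step 3 shows. Extra noise needs mixed scales, which the article neither states nor rules out. This part stands.
- **No bias between arms.** A reader might also infer that regression to the mean under a baseline-fixed site biases the comparison. The arms are randomized and blinded and the aim is a contrast between them, so an equal rise in both is expected to cancel. This part stands too.
- **The dilution needs unequal effects.** Nothing in the article says that BHH10 acts at one site only, an equal effect comes through intact, and the inputs are assumed. This limits the size of the point but does not remove it: nothing in the article says that the two sites respond alike, and the loss of attribution to a site holds whenever the lower site differs between women or visits.
- **A condensed article.** The full protocol may fix site, side and scale, and the plural wording could mean the lowest reading at each site. This is possible, but the article does not merely leave the matter open. It states a rule, and that rule as most naturally read does not hold the site constant. If separate site results were meant, the remedy only makes that explicit.

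**Conclusion.** The point holds as a defect in the definition of one secondary endpoint. Under the most natural reading, the femoral change cannot be attributed to the neck or the total hip, and an effect mainly at one site is understated: a true 0.30 SD units shows as about 0.00 to 0.13 (hip only) or 0.12 to 0.28 (neck only). These figures rest entirely on the assumed between-site gap, its spread and the scan error, and on an effect at one site alone; with an equal effect at both sites nothing is lost.

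The documents do not support the stronger claim that the result is partly an artefact or that the comparison of arms is biased. They also give no reason to doubt the lumbar primary endpoint or the sample size on this account. The harm is lost interpretability and possibly lost sensitivity, not a false positive finding.

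**What to change.** Before unblinding, delete the lowest-value rule and define two separate secondary endpoints: change in femoral neck BMD and change in total hip BMD from visit 1 to visit 5, each in g/cm2 and each at the same site and side at both visits. Name one of them in advance as the main femoral endpoint. The tests already planned for continuous secondary endpoints can be kept.

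No new measurement should be needed, since the present rule already requires a value at both sites. The cost is one additional secondary test and a late amendment: recruitment ended in April 2018, and the latest protocol version (2.7) dates from August 2017. If the full protocol already fixes site and scale, it is enough to state that rule in the analysis plan and the final report.
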